## **9. Reporting of adverse events**

9.1 Anticipated adverse events: collected, recorded in a timely manner and reported regularly to the Ethics Committee.

9.2 Unintended adverse events: timely collection, recording and regular reporting to the Ethics Committee, assessment of risk, the investigator will assist the preparation organization to write a safety report to the institutional ethics committee and inform all investigators, and amend the protocol and informed consent form if necessary. The protocol and consent form should be amended and the investigator's manual should be revised.

9.3 Serious adverse events: If any serious adverse event or significant AE occurs, whether or not it is related to the study intervention and whether or not the intervention has been performed, the investigator should report the event to the institution, the ethics committee, the preparation organization, the Beijing Municipal and National Health Organization, and to the investigator within 24 hours of knowledge. The clinical research organization ensures that all reporting procedures required by laws and regulations are met. The investigator should document in the

source material when, how, and to whom the serious adverse event was reported.

#### **10. Management and reporting of pregnancy events during the study period**

In the event that a pre-menopausal female subject experiences a pregnancy during the study, the investigator should immediately discontinue the subject's clinical. The Investigator shall communicate scientifically and rigorously with the subject based on the information about the stem cell preparation and inform her of the possible effects and risks of the stem cell preparation on the pregnant woman and the fetus. The investigator should complete a "Pregnancy Report Form" within 24 hours of confirmation of pregnancy in a female subject of childbearing potential. The report should be made to the institution, the ethics committee, the preparation organization, the Beijing Municipality and the National Health Commission.

### **(XVII) Risks and benefits of research**

#### **1. Risks and precautions, treatment plan:**

##### **1.1 Physical risks and treatment:**

(1) Localized dental adverse events: mild inflammatory reactions such as mild gingival redness and swelling; severe inflammatory reactions such as periodontal pocket relaxation and pus overflow, periodontal edema, etc. The researcher followed the clinical periodontal disease diagnosis and treatment routine for symptomatic treatment: for the mild inflammatory reaction of periodontal tissues, local flushing of periodontal pockets can be given; for severe inflammation of periodontal tissues, internal debridement of periodontal pockets and internal

antibiotics are given, and local abscess incision and drainage with mouthwash can be done if necessary.

(2) Local hematoma of injection: manifested as local blood vessel injury, bleeding in the tissue, purplish-red bruise under the mucous membrane or subcutaneous. Principles of prevention and treatment: if local hematoma has already appeared, it can be immediately compressed to stop bleeding, and cold compresses can be applied; subjects should be instructed to apply hot compresses after 48 hours to promote the absorption and dissipation of hematoma. Antibiotics and hemostatic drugs can be given as appropriate.

(3) Systemic adverse events: chills, fever, mild headache, which can subside spontaneously. In rare cases, a generalized allergic reaction may occur, and shock may occur as a result of the allergic reaction. In the event of anaphylaxis, follow the "Anaphylaxis Emergency Procedures". If anaphylaxis occurs in a subject, treatment should be carried out in accordance with the "Standard Practice for Anaphylaxis".

**1.2 Psychological Risks and Management:** Some subjects may experience psychological stress due to a lack of knowledge about DPSCs preparations. If so, the researcher will provide psychological intervention and introduce the current status of stem cell clinical research in China and the world, the possible mechanism of action of the DPSCs preparation in this study, and the expected adverse events in the clinic without reason at any time. And inform the subjects that they can withdraw from the study at any time without any reason, so as to eliminate or alleviate the psychological pressure of the subjects.

**1.3 Risks to society and treatment:** Some subjects may have concerns about the safety of the personal information collected during the study. If so, the researcher will explain to the subjects that their private information will be kept strictly confidential at all times during the study. It is also stated that the subjects' private information will only be provided to the investigators of the project, the Ethics Committee and the State Drug Administration when necessary.

**1.4 Financial risks and management:** Subjects may be concerned about the cost of the study and may be burdened with the cost of lost labor due to participation in the study. The Investigator will inform the subject that periodontal treatment, DPSCs injection therapy, and other periodontal treatment that may have been performed as a result of participation in the study will not be covered by the Investigator. Basic treatment, DPSCs injection treatment, and periodontal clinical indicators, laboratory tests, and CBCT performed for participation in this study will be covered by the subject's group. The investigator affirms that subjects will receive \$300 per visit as a transportation allowance and compensation for missed work for participation in this study. The investigator will be responsible for providing cash payment to the subject at the end of each visit. If the subject can complete all visits in this study, the subject will receive transportation allowance and compensation for lost work for 7 visits, totaling \$2100 per subject.

## **2. Benefit:**

**2.1 Benefit to Subjects:** this study intends to enroll subjects with chronic moderate periodontitis. During the study, the investigator will conduct the oral periodontal examination, laboratory and CBCT examination, and the subjects will obtain their own health-related information. All subjects were screened and enrolled in the study and underwent a full-mouth periodontal foundation treatment (including supragingival scaling, subgingival scraping, and a periodontal treatment), which was beneficial for chronic moderate periodontitis. If subjects were assigned to the DPSCs injection group, after basic periodontal treatment combined with

local DPSCs injection, the subjects' periodontal inflammation may be alleviated or resolved.

**2.2 Benefit to science and society:** In chronic moderate periodontitis, current conventional treatments are barely able to regenerate the defective periodontal tissues. The purpose of this study is to evaluate the safety and efficacy of DPSCs injection in the treatment of chronic moderate periodontitis, and to provide a basis for the development of a standardized clinical protocol for the treatment of chronic moderate periodontitis with DPSCs injection.

The results of this study are summarized in the following table.

## **(XVIII) Sample case report form (see Annex 2: Case Report Form (CRF))**

## **(XIX) Statistical analysis of study results**

### **1. Data management**

This study used paper version of the original medical record book (see Annex 3: "Original Medical Record Book") for data collection, which was conducted by the researcher in accordance with the GCP and the requirements of the study protocol to fill in the original medical record book accurately, timely, truthful, complete and standardized, signed and dated. The present study used Clinflash EDC (Electronic Data Capture) system, which was used for data collection by the entry personnel according to the original medical records. The data were entered into the EDC in an accurate, timely, complete and standardized manner in accordance with the EDC guidelines. eCRFs were completed by a supervisor assigned by the preparation facility. The completed eCRF will be logged into the EDC by the supervisor assigned by the preparation institution at the research center to check the consistency between the eCRF data and the source data, and any problems found can be challenged online at any time. If problems are found, they can be challenged online at any time. The data administrator will manually check the data, and if there is any problem, he/she will send out a query to the researcher for confirmation and answer the query.

After the data review is completed, the principal investigator, data management personnel, statistical analysts, and the preparation organization will jointly review the data and complete the final definition and judgment of the analyzed population. The database is locked by the data management staff after the electronic signature of the principal investigator is completed.

### **2. Statistical analysis**

The statistical analysts of this study were not involved in the screening, inclusion of subjects and subsequent clinical studies. During the course of the study, only blinded to the statistical analysts.

#### **(1) Analyzed Population:**

Statistical analysis datasets for the study results included the full analysis dataset (FAS), the protocol compliance dataset (PPS), and the safety Sexuality dataset (SS).

**Full Analysis Set (FAS):** for all cases that had used the study drug after enrollment and had completed at least one efficacy assessment. cases with at least one efficacy assessment completed after enrollment. The estimation of missing values for the main indicators was performed by the method of LOCF (last observation carrying forward).

**Per Protocol Set (PPS):** a subset of the FAS, all cases that comply with the study protocol,

have good compliance, do not use prohibited drugs during the study period, have completed 6 months of clinical observation, and have completed the CRF;

**Safety Set (SS):** all cases that received the study drug after enrollment and had at least one safety assessment. Cases.

In this study, baseline information was analyzed using FAS and PPS analysis. Primary efficacy indicators, secondary efficacy indicators, etc. were analyzed by both FAS and PPS. However, the conclusions obtained from FAS analysis were the main conclusions. When the conclusions from FAS and PPS are consistent, the credibility of the conclusions can be increased.

In the safety analysis, adverse events and adverse reactions, vital signs, and laboratory indicators were analyzed using SS. subjects who were terminated prematurely due to adverse events and various non-therapeutic reasons were included in the safety analysis.

**(2) Statistical analysis plan:** the analysis of the study results included the description of the distribution of subjects, the balance analysis of baseline indicators, the analysis of efficacy, and the analysis of safety.

Mean, standard deviation, median, quartile, minimum and maximum values were used for the statistical description of the measurement data. Comparisons between groups were performed by ANOVA or Kruskal-Wallis rank sum test, and comparisons in groups were performed by paired t-test or Wilcoxon signed rank test. test for within-group comparisons.

Statistical descriptions of counts and rank data used rate or composition ratio, comparisons of count data used  $\chi^2$  test or Fisher's exact probability method, and comparisons of rank data used Kruskal-Wallis rank-sum test.

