**【Adverse Event Record】**

**【Record of combined medications/treatments】**

**【Intraoral photography】 :** Photographs were taken to record the condition of the oral cavity and treatment sites.

**【Randomized grouping】 :** Before D-2, for subjects who met the enrollment criteria, the investigators gave subjects a randomized grouping number based on the randomized grouping

code provided by the statistician to determine the group of subjects and to select the proposed treatment site.

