**4. verification of inclusion and exclusion criteria:** The researchers screen subjects who meet the inclusion criteria and do not meet the exclusion criteria. Comprehensive assessments are conducted for the enrolled subjects to verify if they meet all the screening and inclusion criteria.

**5. allocation of treatment/randomization numbers:** Once the researchers confirm that the subjects meet all the inclusion criteria during the screening period, they will allocate randomization numbers to the subjects based on the randomization codes provided by the statisticians. This random allocation determines the group assignment for each subject. During the baseline/treatment period, the researchers will once again confirm that the subjects meet all the inclusion criteria and inform them of their final group assignment for enrollment.

**6. study compliance management:** Once subjects receive their randomization numbers and are assigned to the researchers involved in this study, it becomes the responsibility of the researchers to track and follow up with the subjects. The researchers should diligently adhere to the study protocol and informed consent form, ensuring that the subjects fully understand the study requirements and cooperate with the research. They should also regularly remind the subjects of scheduled follow-up appointments through phone calls.

**7. compensation and reimbursement:** Subjects participating in this study will receive a fee of 300 RMB per visit as compensation for transportation expenses and loss of income. The researchers are responsible for providing this compensation in cash to the subjects at the end of each visit. If the subjects are able to complete all the scheduled visits for the study, they will receive a total of 7 compensation payments, amounting to 2100 RMB per subject.

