## **(15) Efficacy evaluation criteria**

The efficacy evaluation was evaluated at D7±1 (telephone follow-up), D30±3, D90±3, D180±5, D360±5 after study treatment.

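### The main efficacy set can lose randomised subjects after the arm is known, and its efficacy-assessment condition has more than one reading

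*Protocol*

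**What the plan says.** Protocol Section (XIX) 2(1) takes the FAS "for all cases that had used the study drug after enrollment and had completed at least one efficacy assessment". A repeated fragment there speaks of "cases with at least one efficacy assessment completed after enrollment". The per-protocol set is "a subset of the FAS, all cases that comply with the study protocol", and the section adds that "the conclusions obtained from FAS analysis were the main conclusions". Missing values are dealt with in the FAS definition itself: "The estimation of missing values for the main indicators was performed by the method of LOCF (last observation carrying forward").

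On timing, Section (V) 4(1), Randomized grouping, says: "Before D-2, for subjects who met the enrollment criteria, the investigators gave subjects a randomized grouping number". Section (9) item 5 says that at the baseline/treatment visit "the researchers will once again confirm that the subjects meet all the inclusion criteria and inform them of their final group assignment". The injection follows on D1. The blinding paragraphs of the summary and of Section (V) 3 keep only the periodontal data collectors and the image measurers blind; subjects and injecting investigators know the arm.

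On assessments, Section (15) opens with: "The efficacy evaluation was evaluated at D7±1 (telephone follow-up), D30±3", and goes on to D90, D180 and D360. The schedule table and Section (15) 2(1) place AL measurement at screening, on D1 before injection, and at D90, D180 and D360. The primary endpoint is AL at D90.

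**The concern.** Both conditions for entering the FAS are met or failed after randomisation. Leaving out subjects who were never treated is usually harmless when nobody who influences that decision can know the allocation. Here the investigator knows the group some days before the injection, re-checks eligibility on D1, and can later withdraw a subject for poor compliance or a protocol violation (Section (16) 1). The subject also knows the arm. The blinded examiners protect the AL measurement, but they do not protect membership of the set in which it is analysed.

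The second condition, at least one efficacy assessment, is not tied to a measurement. Whether a subject lost before D90 is excluded or is counted with a pre-injection AL depends on how those words are read. The primary comparison could come out differently under the different readings, and Section (XIX) 1 leaves the final judgement on the analysed population to a joint review held after the data review is complete.

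**Working it through.** **1. Is there an all-randomised efficacy set?** Section (XIX) 2(1) names three sets. The FAS requires injection and an efficacy assessment. The per-protocol set is part of the FAS. The safety set requires injection and a safety assessment, and serves safety only. So no efficacy set covers all randomised subjects.

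**2. Can membership depend on the arm?** The sequence is: group fixed before D-2, eligibility re-check and disclosure to the subject on D1, injection on D1, first scheduled post-injection AL at D90. A subject can leave the FAS between allocation and injection. Under one reading below, a subject can also leave it during the 90 days before the first AL.

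**3. What does the assessment condition mean?**

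| Reading | Basis | Injected subject lost before D90 |
|---|---|---|
| A post-injection AL | Schedule table; Section (15) 2(1) | Excluded from the FAS |
| The D7 or D30 contact counts | Opening sentence of Section (15) | Included if contacted; no AL is taken at those visits, so LOCF carries a pre-injection AL |
| The D1 pre-injection AL counts | The words after enrollment in Section (XIX) 2(1) | Included; LOCF carries a pre-injection AL |

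The last two readings record no change from the pre-injection value. To see the consequence, let m_c and m_s be the mean AL improvements of cell and saline subjects who have a D90 value, and p_c and p_s the shares lost before D90.

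- First reading: estimated difference = m_c − m_s.
- Other readings, if every lost subject enters: (1 − p_c)·m_c − (1 − p_s)·m_s.
- The second minus the first is p_s·m_s − p_c·m_c.

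This is zero only if the products happen to be equal. With equal improvement m in both arms and p_s = 0.10, p_c = 0.03, it is 0.10m − 0.03m = 0.07m, a difference created by the reading alone.

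**4. How large could the exclusion effect be?** The protocol gives no loss rate, no SD and no target difference, so every input here is an assumption. If a share p of an arm is excluded and those excluded are D SD worse than those kept, the kept mean lies p·D above the full-arm mean. The shift in the difference is D·(p_s − p_c).

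- D = 0.5, 10% against 3%: 0.5 × 0.07 = 0.035 SD.
- D = 1.0, 10% against 3%: 1.0 × 0.07 = 0.07 SD.

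For scale, Section (8) uses a two-sided alpha of 0.05 and power of 0.80 with about 33 per group. By the normal approximation this implies a detectable difference of (1.960 + 0.842) × √(2/33) = 0.69 SD. The shifts are about 5% and 10% of that.

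The range widens if loss is one-sided. With a true difference of zero, subjects removed from one arm of 33 and none from the other, the shift is (k/33)·D:

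| Removed, k | Shift, D = 0.5 to 1.0 | Two-sided type I error |
|---|---|---|
| 3 | 0.05 to 0.09 SD | 5.4% to 6.5% |
| 5 | 0.08 to 0.15 SD | 6.0% to 9.1% |
| 7 | 0.11 to 0.21 SD | 6.9% to 12.8% |

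These are what-if figures, not forecasts.

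**The case against.** The route between allocation and injection is narrow. It lasts only days, the D1 check repeats criteria already passed, and saline subjects are injected too. The AL examiners are blind, and the study is labelled exploratory. All of that stands. It limits the likely size but does not make the set independent of the arm.

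The opening sentence of Section (15) heads a section whose first item is safety, so D7 and D30 may simply be a visit list. That is plausible, and it makes this part a matter of clarification.

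Three stronger inferences are not supported.

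- A reader might infer that the FAS contains only subjects who reached D90. That is one reading. The words after enrollment could admit the D1 pre-injection AL. Section (XX) also has withdrawing subjects examined for periodontal status, though it does not name AL.
- A reader might take a 22% loss rate from the earlier subjects in Section (III), where 14 of 18 had effectiveness data (4/18 = 22%), and assign it to the saline arm. The 18 are pooled over an open study of 8 and a randomised study of 10. For those 10, outcomes are reported for 5 saline subjects at day 90 and 5 cell subjects to the end of follow-up. Nothing shows such a loss under saline.
- A reader might infer that a likelihood or imputation model cures the problem. It does not if loss depends on outcome: subjects with no post-injection AL receive values predicted from those who stayed.

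**Conclusion.** The point holds as a modest, inexpensive correction. By the protocol's own definition, the set that carries the main conclusion is not the randomised set. Because the trial is open, entry to it can depend on the arm. The efficacy-assessment condition has at least three readings, which treat subjects lost before D90 differently. This is fixed in the protocol text and is not a detail left to an unseen analysis plan.

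Neither the size nor the direction of any bias can be established from the protocol. The 0.035 to 0.07 SD figure rests on assumed exclusion of 10% against 3% and on those excluded being 0.5 to 1 SD worse than those kept. It would be small beside the 0.69 SD that 33 per group can detect. The larger figures need one-sided losses for which the protocol offers no evidence. The documents do not show that the primary result will be biased. They show that it is not protected.

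**What to change.** - In Section (XIX) 2(1), define the primary efficacy set as all randomised subjects, analysed in the arm allocated, whether or not injected or later assessed.
- Keep the present FAS as a sensitivity set and the safety set for safety.
- Define an efficacy assessment as a post-injection Florida-probe AL reading, and reconcile Section (XIX) 2(1) with the opening sentence of Section (15).
- For a missing D90 AL, replace LOCF of a pre-injection value with a baseline-adjusted likelihood or multiple-imputation model.
- Add a sensitivity analysis in which lost subjects are assumed to do worse than the model predicts, by an amount varied separately in each arm, because the model alone does not remove bias from outcome-dependent loss.

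The cost is wording and a little more analysis; no subject or visit is added, and the total stays at 33 + 33 + 30 = 96. The downside is that a few subjects contribute model-based values only. A D90 AL reading from subjects who withdraw but agree to be measured would help more than any model, at the cost of keeping that visit for them.

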| Effectiveness evaluation | 
① Primary efficacy measures
 
 
■ Oral clinical testing indicators: at screening periods, pre-treatment periods, and follow-up periods D90±3, D180±5, D360±5, examination was performed using a Florida probe, and the measurement of D90±3 was used as the evaluation endpoint.
 
■ attachment level AL (Periodontal depth PD + gingival recession GR).
 
 
② Secondary efficacy indicators
 
 
■ Imaging test indicators: at screening periods and follow-up periods D90±3, D180±5, and D360±5, examinations was performed using a Florida probe, and the screening periods was used as baseline, D180±5 measured value was used as the evaluation endpoint.
 
• Changes in periodontal defect height at 3, 6, and 12 months after the end of treatment compared with baseline (CBCT measurements, change of periodontal defect height = difference in distance from the cemento-enamel to the top of the alveolar ridge).
 
• Changes in mean alveolar ridge density at 3, 6, and 12 months after the end of treatment compared to baseline (CBCT measurements).
 
■ Oral clinical testing index: at screening periods and follow-up periods D90±3, D180±5, D360±5, using Florida probe for examination, use the measurement of D90±3 as the evaluation endpoint.
 
• PD compared to baseline;
 
• Periodontal healing compared to baseline (probing bleeding index BOP, gingival recession GR, tooth mobility TM).
 
 |

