| 2   | Inclusion /Exclusion Criteria                                                                                                     |                                                                                                                  | ×                           | ×                                      |                           |                                                           |                   |                   |                     |
| 3   | Demographic information                                                                                                           |                                                                                                                  | ×                           |                                        |                           |                                                           |                   |                   |                     |
| 4   | Medical history information                                                                                                       |                                                                                                                  | ×                           |                                        |                           |                                                           |                   |                   |                     |
| 5   | Vital signs: respiration, heart rate, blood pressure (systolic, diastolic), temperature (axillary), clinical condition assessment |                                                                                                                  | ×                           | × (Before / 2h±30 min after injection) |                           | × (Double DPSCs injection group 2h±30min after injection) |                   |                   |                     |
| 6   | Periodontal clinical indicators: AL, PD, BOP, GR, TM                                                                              |                                                                                                                  | ×                           | ×                                      |                           |                                                           | ×                 | ×                 | ×                   |

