## 2. Efficacy evaluation index

### (1) Primary efficacy measures

- **【Oral clinical testing indicators】** During the screening period, before administration, and follow-up period, D90±3, D180±5, and D360±5 were examined with Florida probe, and the measured value of D90±3 was used as the evaluation endpoint.  
Periodontal attachment level AL (PD+GR).

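### No AL reading is scheduled between injection and D90, so LOCF normally fills a missing primary endpoint with a pre-treatment value

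*Protocol*

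**What the plan says.** Protocol section (XIX), Statistical analysis, Analyzed Population, puts into the full analysis set (FAS) subjects who received study treatment and had one or more efficacy assessments. It then fixes the handling of missing data: "The estimation of missing values for the main indicators was performed by the method of LOCF (last observation carrying forward". FAS conclusions are the main ones, and agreement with the per-protocol set (PPS) is said to make them more credible. The PPS is limited to subjects who, among other conditions, "have completed 6 months of clinical observation, and have completed the CRF".

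The primary measure is AL, the sum of probing depth and gingival recession. Section (15) says "the measured value of D90±3 was used as the evaluation endpoint", and the synopsis agrees: "and the measurement of D90±3 was used as the evaluation endpoint".

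In the visit schedule table, the row "Periodontal clinical indicators: AL, PD, BOP, GR, TM" is marked at screening, D1, D90, D180 and D360, and is blank at D7 and D30. Section (15), however, opens with a wider list: "The efficacy evaluation was evaluated at D7±1 (telephone follow-up), D30±3, D90±3, D180±5, D360±5 after study treatment".

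**The concern.** LOCF needs an earlier post-treatment value to carry. Here the primary endpoint is itself the first scheduled post-treatment reading, so the rule becomes baseline carried forward. All subjects receive scaling and root planing, so some improvement is expected in every arm, and the imputed value denies it.

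The affected analysis is the one declared to give the main conclusions. Subjects and injecting investigators are not blinded, and only the double-injection arm has a second procedure, at D30. Unequal missingness between arms is therefore plausible, and imputed values would be analysed as if observed.

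**Working it through.** **Step 1. Where AL is measured** (schedule table; visit lists in sections (V) 4 and (XX)).

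| Time | AL probed? |
|---|---|
| Screening | yes |
| D1, before injection | yes |
| D7 | no (telephone: adverse events, medication) |
| D30 | no (vital signs, laboratory tests, adverse events, medication) |
| D90 | yes (primary endpoint) |
| D180 | yes |
| D360 | yes |

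Scheduled AL readings after injection and before D90: 0. The list of assessments for unplanned visits in (XX) does not name probing either.

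**Step 2. What the D1 reading precedes.** In section (V) 4 (2), probing is listed before the basic treatment of the study-tooth area and before the injection. The synopsis places subgingival scaling of that area on D1. By visit order, the carried value precedes both. With D1 as baseline, the imputed improvement is exactly zero.

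**Step 3. Who is affected.**
- D90 missing, D180 or D360 present: the subject is in the FAS on any reading. The D1 value is used and the later ones are ignored.
- No AL from D90 on, and the D7 call or D30 visit counts as an efficacy assessment: in the FAS with the pre-treatment value.
- No AL from D90 on, and an AL reading is required: not in the FAS, so LOCF does not apply.

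**Step 4. Bias.** Let m be the share missing in an arm and mu the mean improvement those subjects would have had at D90 (1 = cells, 0 = saline). Zero imputation lowers each arm's mean by m·mu, so

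bias in the difference = -(m1·mu1 - m0·mu0).

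- Equal m, with missing subjects improving on average like the rest of their arm: a true difference δ becomes (1 - m)δ. At m = 10% that is 0.90δ.
- Equal mu in both arms: bias = -(m1 - m0)·mu. Assuming mu = 1.0-1.5 mm and a gap of 5-10 points, the size runs from 0.05 × 1.0 = 0.05 mm to 0.10 × 1.5 = 0.15 mm, against the arm with more missing data.

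For scale, 5-10 points of 33 subjects is 1.65-3.3, or about 2-3 people. If S were 1 mm (assumption), the standard error of a 33 v 33 difference is √(2/33) = 0.246 mm, so the bias is 0.05/0.246 = 0.2 to 0.15/0.246 = 0.6 standard errors.

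**Step 5. Power with equal missingness.** The arm totals add up: 23 + 10 = 33, 23 + 10 = 33, and 30, giving 96. The 96 cannot be recomputed, because section (8) gives no values for S or δ. Back-solving with a normal approximation at two-sided α 0.05 and power 0.80 for 33 v 30:

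δ/S = (1.960 + 0.842) × √(1/33 + 1/30) = 0.707.

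In units of S, an arm with share m set to zero change has mean (1 - m)mu and variance (1 - m)(1 + mu²) - (1 - m)²mu². The saline mean improvement is assumed to be 0.5 to 1.0 S. Example, m = 10%, saline 0.5, cells 1.207: the variances are 0.9225 and 1.031, the standard error is √(0.9225/33 + 1.031/30) = 0.250, and 0.636/0.250 - 1.960 = 0.59, giving power 0.72.

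| m | Power with zero imputed | Power if those subjects are simply left out |
|---|---|---|
| 0% | 0.80 | 0.80 |
| 5% | 0.76-0.74 | 0.78 |
| 10% | 0.72-0.68 | 0.76 |
| 20% | 0.64-0.56 | 0.71 |

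The last column is Φ(2.802 × √(1 - m) - 1.960). The gap between the columns is the loss due to the imputation rather than to missing data as such.

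**The case against.** A reader might infer that LOCF can only ever carry a pre-treatment value. The documents do not support that. Section (XX) has subjects with adverse reactions followed on the screening indicators, which include AL, and swollen, painful gums within a week count as such a reaction. It also has withdrawing subjects examined for periodontal health. Neither place names AL or says that the reading enters the analysis, but one before D90 is possible. What stands is that none is scheduled.

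A reader might also infer that every early drop-out enters the main analysis as a non-responder. That requires a telephone call or a D30 visit without probing to count as an efficacy assessment. The only support is the opening sentence of section (15), which is followed first by safety indices. Section (16) 1 also allows some subjects, including early withdrawals, to be replaced. On the narrow reading, only subjects who miss D90 but attend later are affected.

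The D1 value is not free of all treatment: full-mouth supragingival cleaning takes place at D-14. Section (V) 4 (2) labels the study-area treatment D-1 and calls it supragingival, although it describes subgingival scaling; the synopsis has subgingival scaling on D1. These passages must be reconciled, but on either day no AL reading after the injection precedes D90.

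The study is labelled exploratory, uses visit payments and telephone reminders, and states no expected drop-out, so missingness may be low. One PPS serves both AL at D90 and CBCT at D180, so six months of observation suits the latter. Both points lower the severity; neither gives LOCF a suitable value to carry.

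**Conclusion.** The concern holds in limited form and should be fixed. Barring an unscheduled reading, the stated rule replaces a missing primary endpoint with a value from before the injection and, by visit order and the synopsis, before subgingival scaling of the study tooth. Real D180 or D360 data are set aside. The schedule alone establishes this.

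Its size is not established. The 0.05-0.15 mm assumes 1.0-1.5 mm improvement in both arms and a 5-10 point missingness gap. The power figures assume δ/S = 0.707, a saline improvement of 0.5-1.0 S, and missingness unrelated to response. With few missing D90 values the effect is small.

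Two further inferences are tempting. One is that LOCF is at least conservative. It is not reliably so: equal missingness shrinks a true effect, but more missing data in the saline arm would favour the cells. The other is that the primary result is invalid. Nothing in the protocol shows that much missing data.

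**What to change.** In section (XIX), delete the LOCF sentence for the primary endpoint and state that:

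- AL at D90 is estimated from a mixed model for repeated measures on the D90, D180 and D360 readings, with baseline AL, phase, treatment, visit and treatment-by-visit. The text should say whether readings taken after other treatment for progression are used, since section (16) 4 allows such treatment.
- Only a post-treatment AL probing counts as the efficacy assessment for entry to the efficacy FAS. The opening sentence of section (15) should be aligned with this.
- Multiple imputation over all treated subjects is a sensitivity analysis. It is needed because the mixed model, with baseline as a covariate, gains no outcome information from subjects with no post-treatment AL, and the clarified FAS leaves them out.

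Secondary: for the AL analysis, define the PPS by a valid D90 reading instead of six months of observation, so that a subject with a valid primary endpoint is not removed for later events.

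Cost: a protocol amendment under section (XXI) 5 and slightly more analysis work. All the readings needed are already scheduled.
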